## Abstract

**Background:**

Substance-related and addictive disorders are among the most common mental disorders in adolescence and young adulthood. Vocational school students are a risk group for problematic substance use and addictive behavior. However, the availability of evidence-based prevention concepts and programs is underdeveloped in the vocational school setting.

**Methods/design:**

A two-arm cluster randomized waitlist-controlled trial will be conducted to evaluate the effectiveness of an app-based intervention to decrease substance use, gambling, and digital media use in vocational school students in Germany. Vocational students will participate in an app-based intervention that is designed to support voluntary commitment to abstain from or reduce substance or digital media use over a period of 2 weeks. The “education-as-usual” control arm will have access to the intervention after data collection is completed. One of the primary outcome measures will be the use of alcohol, nicotine, and digital media 30 days after the intervention. Several secondary outcome measures will also be included, such as cannabis consumption, gambling, symptoms of stress, physical activity, mindfulness, well-being, impulsivity and sensation seeking, and readiness to change. A total of 4500 vocational students from 225 classes will be recruited and randomized across three German federal states.

**Discussion:**

This study protocol describes the design of an RCT testing the effectiveness of an app-based intervention to reduce addictive behaviors in vocational school students. It is expected that this approach will be feasible for and effective in the vocational school setting and that the study provides comprehensive information on the key factors involved in temporary abstaining or reducing substance or digital media use.

**Trial registration:**

German Clinical Trials Register DRKS00023788. Registered on 20 January 2021

## Administrative information

Note: The numbers in curly brackets in this protocol refer to SPIRIT checklist item numbers. The order of the items has been modified to group similar items (see http://www.equator-network.org/reporting-guidelines/spirit-2013-statement-defining-standard-protocol-items-for-clinical-trials/).

## Introduction

### Background and rationale {6a}

Substance-related and addictive disorders typically have their onset in early adolescence and belong to the most common psychological disorders among emerging adults [1, 2]. In Germany, the group of 18- to 20-year-olds has the highest risk of addiction diagnoses regarding alcohol (6.4%), cannabis (1.5%), amphetamines (0.4%), and cocaine (0.3%) according to population-based survey data [3]. Research has consistently shown that the period of emerging adulthood [4] is not only associated with a readiness to engage in risky and unhealthy behavior such as substance abuse but also with limited capacities for self-regulation and (substance use-related) habit formation [5].

The proportion of young people affected by addictive behaviors increases if non-substance-related or “behavioral” addictions, particularly Internet-related disorders, are also taken into account [6]. Gambling disorder and (screen-related) gaming disorder seem to be similar to substance-related addictive disorders regarding their clinical appearance, etiology, comorbidity, and therapeutic responsiveness [7, 8]. Moreover, they are of increasing epidemiological relevance (even more so during the current COVID-19 pandemic conditions, see [9]) and have therefore recently been included in the revised classification of Substance-Related and Addictive Disorders in the 11th edition of the International Classification of Diseases (ICD-11) of the World Health Organization (WHO) (see [10]).

The school setting is particularly relevant for prevention efforts as it represents a central developmental context where a large number of individuals can be reached with comparatively little effort [11]. The majority of evaluated school-based preventive intervention programs apply only to regular schools, while there has been a lack of comparable programs for vocational schools [12]. However, in Germany, a substantial proportion of young people leaves the regular school system during adolescence and starts a vocational education, typically from the age of 16 [13, 14]. Vocational education in Germany largely takes place in the “dual system,” in which trainees are employed in a company and complete the practical part of their training there, while also attending vocational school, where the theoretical part of the training takes place.

Recent studies suggest that vocational students represent an important target group for prevention efforts and health promotion. In a survey including 5688 German vocational students, 40.5% of the participants reported a positive screening result for problematic alcohol use and 3.6% reported a level of cannabis use that puts them at serious risk for addiction [15]. The percentage of vocational students that reported daily smoking (41%) was 2.4 times greater than their age-matched peers in the general population. With regard to addictive behaviors such as online and offline gambling and digital media use, there are currently no data available that estimate the specific risks of vocational students. However, surveys indicate that media-related problems are particularly widespread among adolescents and young adults of typical vocational school age [6, 16].

A promising school-based prevention approach is a voluntary commitment to abstain from or reduce habitual behaviors like substance use. For example, one of the most widespread programs for the prevention of smoking in secondary schools in Germany is the smoke-free class competition “Be smart – don’t start.” At the core of the program is a joint voluntary commitment of the school class to not smoke for a period of 6 months. It focuses on influencing social norms, promoting self-regulation, and addressing social influences by deploying cognitive-behavioral intervention techniques [17]. Overall, the evidence based on process and rigorous outcome evaluations, long-term and iatrogenic effects, and cost-benefit efficiency are convincing, even in comparison with other programs (see [18]). An adaptation of this approach has also been shown to be effective in the prevention of binge drinking among older adolescents in the regular school setting in a randomized study [19]. Furthermore, the results of a recent controlled study in Germany [20] suggested that a 20-min reduction of daily social media use over a period of 2 weeks is positively associated with well-being and a healthier lifestyle among students. Specifically, the reduction in social media use not only reduced social media use intensity and the level of addictive symptoms but also the amount of daily smoked cigarettes over a period of 3 months.

### Objectives {7}

The present study aims to transfer the approach of voluntary abstinence to the vocational school setting and to evaluate the feasibility and effectiveness of this approach using a randomized design. It is expected that the intervention will increase awareness of habitual behaviors (e.g., substance and digital media use) and lead to a measurable reduction of these behaviors even after the end of the abstinence or reduction period.

### Trial design **{8}**

The current study uses a cluster-randomized controlled exploratory trial with two arms, an intervention group (IG), and a waitlist control group (CG) with pre-post assessments. All study participants will be randomly assigned to one of the two groups on the class level (Fig. 1).

**Fig. 1 Fig1:**
[figure not shown]
Consolidated Standards for Reporting Trials (CONSORT) diagram: study design and participant flow

## Methods: participants, interventions, and outcomes

### Study setting {9}

The study will be conducted in vocational schools in the three German federal states of Schleswig-Holstein, Bavaria, and Hamburg. Schools were not systematically selected to represent the complexity of the vocational school system in Germany [14]; therefore, they vary in size, regional area, urbanicity (rural vs. urban), and vocational areas (e.g., business administration, industrial-technical professions, personal services).

### Eligibility criteria {10}

All vocational students will be eligible to participate in the study if they or one of their legal guardians (if the student is under the age of 16) provide written informed consent.

The age range of students attending vocational schools in Germany is broad. The mean age of students when starting vocational training is 19.7 years; approximately 11% of the students are aged 16 years or younger or 24 years or older [14].

### Who will take informed consent? {26a}

Trial participants and, if under the age of 16, their legal guardians will be provided with sufficient verbal and written information about the study’s purpose and procedures, information on confidentiality and data protection procedures, possible advantages and disadvantages of participation, and the option to withdraw from the study at any time and without any given reason. They are informed that participation in the study is completely voluntary. Written informed consent will be provided to and obtained from all participants prior to study enrollment by members of the study team.

### Additional consent provisions for collection and use of participant data and biological specimens {26b}

The consent includes the participant’s agreement to the collected data being used and published in an anonymized form for research purposes. This trial does not involve collecting biological specimens for storage.

### Interventions

#### Explanation for the choice of comparators {6b}

The comparator is an education-as-usual waitlist control group. All participants will be randomly assigned to either the app-based intervention group or the control group. The participants of the control group will continue routine activities during the (approximately) 6-week waiting period. This time frame was chosen because the intervention (use of the Mzo app) lasts 2 weeks and the primary trial outcomes concern past-month substance and media use. After post-assessment, participants of the control group will receive full access to the intervention app. Crossover and influence from peers in the experimental group can be considered low due to class-wise randomization and the nature of the vocational school setting (e.g., presence at school varies for each vocational area, and students are not present at school on a daily basis).

#### Intervention description {11a}

“Meine Zeit ohne” [*my time without*] (MZo) is an app-based intervention that aims to encourage users to voluntarily abstain from an individually relevant habitual behavior or to reduce it to a degree that is subjectively considered significant or a “challenge” for a period of 2 weeks. After downloading the app (downloadable for devices running on iOS 11.0 or higher/Android 6 or higher) and log in with a password, students can set their individual challenges. For the next 2 weeks, participants receive push notifications on a daily basis and are asked for feedback about whether they have reached their goal of the preceding day. MZo primarily targets consumption behavior (both substance-related and non-substance-related behavior, i.e., digital/screen-based media-related behavior such as gaming and/or social media use).

#### Criteria for discontinuing or modifying allocated interventions {11b}

Participants in the intervention group can discontinue the use of the intervention app at any time by deleting the app from their mobile devices. The intervention, i.e., the use of the app, does not require any contact with the study team.

#### Strategies to improve adherence to interventions {11c}

The implementation of the MZo challenge is entirely app-based. The effort required to use the app can be considered minimal. Adherence to the intervention is facilitated by an easy-access procedure (log-in and user authentication are only required once after the download of the app) and daily push notifications. The app provides the opportunity to choose individual behavior change goals from a broad spectrum including an undefined goal category which can be specified by the individual user.

#### Relevant concomitant care permitted or prohibited during the trial {11d}

Participation in the current trial has no impact on possible concomitant care during the time of the trial.

#### Provisions for post-trial care {30}

All participating schools are provided with contact information of the study sites and can access evidence-based information material on substance use and substance use prevention via the project website.

### Outcomes {12}

#### Primary outcomes

Outcome measures at each time point are shown in Fig. 2. One of the primary outcomes is self-reported use of alcohol, nicotine (cigarettes and/or electronic cigarettes), and digital media (gaming and social media) in the past month. Measures for alcohol use are based on [21] and include frequency of drinking (1 = “never” to 5 = “four times a week or more”), quantity of alcoholic drinks on a typical drinking day (1 = “1 or 2 alcoholic drinks” to 5 = “10 or more alcoholic drinks”), and frequency of binge drinking (more than 6 alcoholic drinks on one occasion; 0 = “never” to 4 = “daily or almost daily”). Nicotine use is assessed based on students’ reports on the number of days using cigarettes and/or electronic cigarettes and their quantity per day. Problematic Internet gaming is assessed using the Internet Gaming Disorder Scale-Short-Form (IGDS-SF [22];), German version ([23]; 9-items: e.g., “Have you continued your gaming activity despite knowing it was causing problems between you and other people?”; 1 = “never” to 5 = “very often”). Problematic social media use was assessed using an adapted version of the brief version of the Bergen Facebook Addiction Scale (BFAS [24];; German version: [25]). The scale consists of 6 items (e.g., “Felt an urge to use social media more and more”; 1 = “very rarely” to 5 = “very often”). All primary outcome measures (in their German versions) have been used in previous studies and can be considered psychometrically valid.

**Fig. 2 Fig2:**
[figure not shown]
Standard Protocol Items: Recommendations for Interventional Trials (SPIRIT) diagram detailing the trial activities and measures and their timing

#### Secondary outcomes

A number of individual-level secondary outcome measures were selected based on their health-related relevance and associability with the conceptual intervention approach. These outcomes are as follows:
Problematic cannabis use (Severity of Dependence Scale (SDS), 5 items [26]; German version: [27])Problematic gambling (Brief Biosocial Gambling Screen (BBGS), 3 items [28])Psychological stress (Depression Anxiety Stress Scales 21 (DASS-21), subscale stress, 7 items [29]; German version: [30])Impulsivity and sensation seeking (Substance Use Risk Profile Scale (SURPS), subscales impulsivity and sensation seeking, 2 items each [31])Mindfulness skills (Child and Adolescent Mindfulness Measure (CAMM), 10 items [32])Physical activity (past month frequency of physical activity/sports, single item, self-constructed)Positive mental health (Positive Mental Health Scale (PMH), 9 items [33])Life satisfaction (L1, General Life Satisfaction Short Scale, single item [34], German version [35])General self-efficacy (Short Scale for Measuring General Self-efficacy Beliefs (ASKU), 3 items [36])Readiness and confidence to quit or reduce the use of alcohol, nicotine, cannabis, gaming, social media, and gambling (readiness/confidence ruler (10 = “not at all ready/difficult to change” to 100 = “very ready/difficult to change”) assessing readiness and confidence in quitting or reducing each behavioral outcome; based on [37])

For a list of included secondary outcomes, see Fig. 2. Additionally, we assess socio-demographic data (age, gender, migration background, socio-economic status), progress of vocational education, educational sector, and frequency of in-school education.

#### Participant timeline {13}

In Fig. 1, trial procedures from enrollment to the end of the trial are illustrated.

#### Sample size {14}

The sample size is calculated to detect a minimum relative difference of 20% between both groups at post-assessment. This effect was based on previous studies on the effectiveness of substance use prevention programs [11, 19] and takes a clustered data structure and an intra-class correlation (ICC) of 0.032 as well as a drop-out rate of 30% on the student level into account (based on [15]). The required sample size for 80% power to detect between-group differences at the 0.05 level is 4500 students (2250 students per condition) from 225 classes.

#### Recruitment {15}

The three study sites cooperate with local school supervisory authorities, which support the project and allow the recruitment of a convenient sample of vocational schools. Class teachers and other school staff (such as school social workers) at those schools are informed about the study in teacher conferences. This information includes access to the project website which features explanation videos about the MZo app and the implementation of the study. Teachers will be provided a login code to test the MZo app prior to implementation in their class. If teachers decide to participate in the study, two appointments for data collection and for the introduction of the intervention will be scheduled. Consent to participate in the study on the student level has to be provided prior to baseline assessment.

### Assignment of interventions: allocation

#### Sequence generation {16a}

Randomization will be performed at the class level. The randomization sequence has been created [38] using the program “Randomization in Treatment Arms” (https://www.evidat.com/rita). Classes of vocational schools will be stratified by class characteristics and paired into dyads of similar classes. The first member of a dyad will have a 50% chance to be assigned to the intervention group, and the remaining class will automatically be assigned to the other trial arm.

#### Concealment mechanism {16b}

In the temporal order of study inclusion, allocation of classes will be made according to the randomization plan to either the MZo intervention or the control group. Participants, teachers, and schools will have no influence on the allocation process and assignment of classes to either group, but they will not be blind to randomization.

#### Implementation {16c}

Random allocation of classes within schools to either the MZo intervention or the control group using the randomization plan takes place at each study site under the responsibility of the local study team. All students who give their written consent (electronically) to participate in the study will be enrolled. Unique identifiers are generated using an ID-generator software and will provide access to the electronic assessment portal. The flow diagram of the study design is depicted in Fig. 1.

### Assignment of interventions: blinding

#### Who will be blinded {17a}

All participants, teachers, and schools will be blinded to the randomization and allocation process. However, they will not be blind to the MZo intervention, as participants of the control group will be informed that they will receive access to the MZo app after post-assessment. Data analysts will be blinded.

#### Procedure for unblinding if needed {17b}

The design is open-label with only data analysts being blinded so unblinding will not occur.

### Data collection and management

#### Plans for assessment and collection of outcomes {18a}

Data will be collected class-wise in schools. The baseline assessments will take place directly before the intervention and the post-assessments at least 30 days after the end of the intervention. All measures are assessed via the online system “SoSci Survey,” program version 3.2.12 (15.02.2021). All collected data is entered using participants’ personal smartphones. If individual smartphones are unavailable or not functioning due to technical problems, the study teams will provide tablets to ensure data collection. To guarantee a smooth online data assessment, the study teams will also provide a portable LTE router for a stable Internet connection in the classroom if necessary. As for the MZo app and the online assessment portal, compatibility with current Android and iOS devices is given.

#### Plans to promote participant retention and complete follow-up {18b}

According to their allocation, study participants will complete the online questionnaires in class. Unique identifiers are distributed by the study team and can be used to access the questionnaire for pre- and post-assessments. The same identifier can also be used to log in to the MZo app. To maintain high retention rates between pre- and post-assessments, participants are encouraged to take a smartphone picture of their unique identifier. To maximize data completeness, vocational students who are absent from school on the day(s) of the assessment will be contacted in a coordinated approach by their teachers.

#### Data management {19}

Online assessment data will automatically be transferred to a local server at the study site in Kiel (SH), minimizing errors of data entry. All participant data is handled in accordance with the General Data Protection Regulation (GDPR). All data will be maintained confidentially before, during, and after the trial and is stored securely at the study site in Kiel with access only by dedicated study team members.

#### Confidentiality {27}

All data is collected using 6-digit unique identifiers to access the online questionnaires. The first two digits of this code identify the specific school, the next two digits identify a particular class, and the last two digits that identify an individual participant are randomly distributed. Single individuals cannot be identified.

#### Plans for collection, laboratory evaluation, and storage of biological specimens for genetic or molecular analysis in this trial/future use {33}

No biological specimens will be collected.

## Statistical methods

### Statistical methods for primary and secondary outcomes {20a}

Analyses will account for the clustering of individuals in school classes and will be reported following CONSORT standards. Trial variables will be analyzed by the intervention arm, into which participants were randomly assigned. Continuous outcomes will be reported for each trial arm using means and standard deviations, and binary outcomes will be reported for each trial arm using numbers and percentages. The main intervention effects will be tested by means of logistic or linear multi-level/random effects regression models with the levels “classes” and “individuals,” whereby group and time variables as well as the interaction term group × time are used. Primary between-group analyses will be adjusted for baseline scores of the outcome variable, relevant covariates (baseline prognostic factors that are theoretically associated with outcomes, including, but not limited to age, gender, and migration background as well as the personality traits sensation seeking and impulsiveness), and those variables used to stratify randomization.

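### The primary analysis combines a group × time test with adjustment for the same outcome's baseline score: incompatible as one model, undecided as two

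*Protocol article*

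**What the plan says.** The section on statistical methods for primary and secondary outcomes {20a} has two consecutive sentences on the model.

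- The first tests the main intervention effects with "logistic or linear multi-level/random effects regression models with the levels" of classes and individuals, "whereby group and time variables as well as the interaction term group × time are used".
- The second states: "Primary between-group analyses will be adjusted for baseline scores of the outcome variable", and adds prognostic covariates and the stratification variables.

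The trial design section {8} describes an intervention group and "a waitlist control group (CG) with pre-post assessments", so there are two occasions per student. The missing-data section {20c} plans multiple imputation, so each analysed data set would hold both values for every student. The sample size section {14} reads: "The sample size is calculated to detect a minimum relative difference of 20% between both groups at post-assessment".

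Nothing in {20a} says that the two sentences describe different models, or that the outcome is restricted to the post value.

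**The concern.** A group × time term with two occasions needs the baseline value as an outcome row. Adjustment for the baseline score belongs to a model whose only outcome is the post value. If both go into one equation, the baseline rows are predicted by themselves. Three consequences follow.

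- The adjustment may do nothing for the tested term.
- The residual variance, and so the standard error, may be too small.
- In a logistic model, the odds ratio may lose its meaning as a baseline-adjusted effect.

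If two equations were meant, a change analysis and a baseline-adjusted post analysis both claim to be primary. Either way, the test of the main intervention effect is not fixed.

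**Working it through.** **Inputs from the protocol article.** Two occasions; "an intra-class correlation (ICC) of 0.032"; "a drop-out rate of 30% on the student level"; 4500 students in 225 classes. That is 4500/225 = 20 per class and 20 × 0.7 = 14 completers, with about 112 classes per arm. The article gives no precision for this model, so there is no figure of its own to reproduce.

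**Assumed, because not given.** Student-level pre-post correlation r (0.3 to 0.8) and correlation of a class's effect between the two occasions, the class autocorrelation (0.5 to 1.0).

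**1. The baseline adjustment cancels (linear outcomes).** The baseline score is constant over a student's two rows. With both rows present, group × time is orthogonal to it, and the estimate is the raw difference in change. In simulation at r = 0.5, its empirical SD was 0.0355 both with and without the covariate. With n students per arm and unit variance:
- difference in change: 4(1−r)/n
- post value adjusted for baseline: 2(1−r²)/n
- ratio: 2/(1+r) = 1.54, 1.33, 1.25, 1.18 and 1.11 at r = 0.3, 0.5, 0.6, 0.7 and 0.8.

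This is the student-level ratio. With class effects included, simulated variance ratios at r = 0.6 were about 1.10, 1.18 and 1.25 at class autocorrelation 1.0, 0.8 and 0.5.

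**2. Standard error of the literal model.** The baseline slope is pooled over rows where it is 1 and rows where it is r, giving b = (1+r)/2. The residual variances are then
- baseline rows: (1−r)²/4
- post rows: (1−r²) + (1−r)²/4
- average: (1−r)(3+r)/4.

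The model therefore gives the interaction a variance of (1−r)(3+r)/n, against a true 4(1−r)/n. Model SE over true SE is √((3+r)/4):

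| r | SE ratio | Type I error |
|---|---|---|
| 0.3 | 0.91 | 7.5% |
| 0.5 | 0.935 | 6.7% |
| 0.6 | 0.95 | 6.3% |
| 0.7 | 0.96 | 5.9% |
| 0.8 | 0.975 | 5.6% |

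A student random intercept does not repair this. A student's two residuals have covariance −(1−r)²/4 (−0.04 at r = 0.6), so the intercept variance is estimated at zero, as the simulations showed.

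**3. With class-by-time variation.** The class intercept cancels from a change contrast, but a class-level change does not. The true variance is 4·ICC·(1−autocorrelation)/112 + 4(1−r)(1−ICC)/(112·14). At r = 0.6:
- autocorrelation 0.8: 0.000229 + 0.000988, so true SE 0.0349. Mean model SE in simulation was 0.0300; the ratio 0.86 implies 9.2%. Simulated type I error was 8 to 9%.
- autocorrelation 0.5: 0.000571 + 0.000988, so true SE 0.0395. Mean model SE was 0.0302; the ratio 0.76 implies 13.4%. Simulated type I error was 13 to 14%.
- autocorrelation 1.0: simulated type I error 6.5%.

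The post-only model with baseline as covariate gave 4.8%, 5.4% and 5.4% at autocorrelation 1.0, 0.8 and 0.5 (2,500 runs each).

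**4. Logistic outcomes (illustration without random effects).** The control rate is assumed to be 40.5%, the survey figure for problematic alcohol use in the background section. A 20% relative reduction gives 0.405 × 0.8 = 0.324. The marginal OR is (0.324/0.676)/(0.405/0.595) = 0.70. At a 0/1 pre-post correlation of 0.49:
- stacked model with baseline covariate: interaction OR 0.46
- post-only model adjusted for baseline: 0.63
- stacked model without the covariate: 0.70.

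At correlations 0.33 and 0.64, the first two are 0.53 against 0.675 and 0.35 against 0.55. With no effect, every version gives 1.00.

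**The case against.** **Two analyses may have been meant.** The article never says that the baseline score enters the same equation as the group × time term. On that reading, the cancellation and the odds-ratio distortion disappear. This stands as a reading, but it leaves two primary estimates and no rule for choosing between them.

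**The levels may be adequate.** A reader might infer that the plan has no term for the two occasions within a student. The text does not support that: naming individuals as a level ordinarily means a student intercept, with occasion as the residual. The understated standard error depends on the baseline covariate being in the stacked model. Without it, a class-only model overstates the standard error (simulated ratios 1.39 to 1.90), and a class-plus-student model is about right unless classes change over time. Its type I error is 5.0% at class autocorrelation 1.0, 6.2% at 0.9 and 7.5% at 0.8 (r = 0.6). The waiting period is only about six weeks, so high autocorrelation is plausible. A class × time term may also be left to an analysis plan, so its absence from an article is not itself an error.

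**The odds ratios are on different scales.** A reader might infer that binary effects are overstated by the full gap from 0.63 to 0.46. Odds ratios are not collapsible. A student-intercept longitudinal logistic model without the baseline covariate gives 0.505 in the same scenario. On the log scale that is ln(0.631/0.505) = 0.22 of a gap of ln(0.631/0.459) = 0.32, so much of the gap is a change of estimand. It creates no false positives, and most primary measures are frequencies, counts or scale scores rather than binary.

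**Unadjusted analyses are planned.** They are sensitivity analyses. For linear outcomes, dropping the baseline covariate leaves the group × time estimate unchanged and alters only its standard error.

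**Conclusion.** The concern holds as a specification error in the primary analysis. The cancellation in linear models is algebraic and needs only both rows per student. The cost in variance, 2/(1+r) at student level, depends on r.

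The literal model's standard error is too small for any r below 1. Without class-by-time variation the shortfall is modest: about 2 to 9%, type I error about 5.6 to 7.5% for r from 0.3 to 0.8. The larger figures, about 8 to 9% and 13%, rest on assumed class autocorrelations of 0.8 and 0.5 at r = 0.6. They show sensitivity and are not established error rates of this trial.

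For any logistic outcome, the interaction odds ratio cannot be read as a baseline-adjusted effect. The documents do not support calling the whole gap bias.

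If two models were intended, these magnitudes do not apply as stated, but the plan then does not say which estimate decides. Both readings call for the same correction.

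**What to change.** State one primary model in {20a}: a linear or logistic mixed model with the post-assessment value as the only outcome. Fixed effects are arm, baseline value of that outcome, the stratification variables and the named covariates, with a random intercept for class. The arm coefficient is the primary test, and group × time is dropped from the primary analysis. This matches the sample size section, which targets a difference at post-assessment.

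If a longitudinal model is kept as a sensitivity analysis, omit the baseline covariate and include student and class × time random effects. A longitudinal model that constrains the arms to a common baseline mean, with those random effects, would also be sound as primary. What matters is that one model is named.

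The cost is a rewording of two sentences, with no new data and no change to the design. It should be settled and documented before the analysts see results by arm.
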